### Data analysis plan

A researcher who is blinded to group allocation will perform the data analysis. All analyses will be performed with SPPS Statistics software (IBM Corp., Armonk, NY, USA). Data will be expressed as frequency and percentages for categorical variables, and mean, standard deviation, range and median for quantitative variables depending on the distribution (normality will be checked with the Shapiro–Wilk test). The statistical significance level will be set at *P* < 0.05.

For the primary outcome of improvement in wound healing the wound area reduction at 8 weeks in the intervention group compared with the standard care group will be tested by a difference of means test. The increase in RESVECH 2.0 [37] score at 8 weeks between both groups will be examined by a difference of means test (*t* test for independent groups or Mann–Whitney test depending if variables adjust to a normal distribution). The effect size will be estimated by Cohen’s *d* statistic. In addition, a repeated-measures analysis (analysis of variance or Friedman test) and a survival analysis (Kaplan–Meier) will be used to analyse the evolution over time.

For secondary outcomes, proportions and categorical variables will be tested using a chi-squared test, and continuous variables will be tested using a mean difference test (parametric or nonparametric).

Analyses will be performed between groups as randomized (an intention-to-treat analysis). Missing data for the outcomes will be tested if they are missing at random; otherwise the last observation carried forward approach will be used for imputation [43]. Furthermore, sensitivity analyses over all the completed cases (a per-protocol analysis) will be performed to check for inconsistencies.

A subgroup analysis by wound type will also be performed to explore whether the effect of the intervention differs for any type of wound according to its aetiology. Moreover, another subgroup analysis by primary care centre will be carried out to check if there are any differences in outcomes according to the centre.

No interim analyses or formal stop-study rules are planned; no harmful problems are anticipated for patients because this new dressing has been previously tested in a series of patients with wounds of various aetiologies without any serious adverse effects [35].

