### Randomization and blinding

Patients (*n* = 54) will be randomized into an intervention group (antioxidant dressing) or control group (standard clinical practice using dressings that create a moist environment). The block randomization scheme was generated using the EPIDAT software. Participants will be randomized to receive antioxidant dressing or standard wound dressing with a 1:1 allocation ratio (Fig. 2) using stratified block randomization with a fixed block size per centre. Once the patient has agreed to participate and has been shown to meet the inclusion criteria, the clinical nurse will open opaque closed envelopes sequentially numbered containing a sheet (folded four times) with the group allocation. Neither the patient nor the clinical nurse is blinded to the treatment received; the data and the wound pictures will be codified and the assessor who evaluates the wound pictures and the data analyst will be blinded to the treatment.

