### Outcomes

The primary outcome is the improvement in wound healing with two end points: 1) an increase in the RESVECH 2.0 scale score [37] (score at baseline minus score at 8 weeks); and 2) a reduction in the wound area (area at baseline minus area at 8 weeks). The RESVECH 2.0 score includes the assessment of the wound area, but we also decided to use the reduction in wound area as a specific end point to have a direct measurement of wound size (despite not estimating the sample size with this outcome because there were no data available from previous studies). Additionally, the values at 2, 4 and 6 weeks for each end point will be calculated. These end points are chosen for the clinical relevance of the antioxidant dressing because this product is well-known for removing the nonviable tissue (necrotic or devitalized) in the wound bed, for promoting the production of granulation tissue and for activation of the healing process [35, 42].

The secondary outcomes are the time to achieve a 50% reduction in wound area, the time elapsed until removal of nonviable tissue from the wound bed, reduction of the wound area, the number of completely healed wounds, the pain level and the area of the wound with bacterial load (clinical signs of infection or measurement of surfaces containing bacteria).

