## Discussion

This randomized clinical trial will be the first to compare the effect on chronic wound healing using an antioxidant dressing with the use of a dressing that creates a moist environment (standard care) in patients with hard-to-heal wounds.

Currently, through the research of scientists, engineers and manufacturers, we are witnessing an increase in scientific knowledge about wound healing; this is associated with the development of products that promote positive results and mitigate negative factors in wound healing. All of these research findings and resources are transferred to clinical practice through evidence-based wound management [44].

The dressing with antioxidant properties has been previously tested in animal models [33] and in patients with acute and chronic wounds of various aetiologies, showing a potential to activate the healing process [35]. The antioxidant effect of NAC may play a role for tissue repair under normal and pathological conditions, thus improving wound healing [28, 42].

In addition, some recently published data point to a positive cost–benefit balance for the treatment of venous ulcers with an antioxidant dressing [24, 36].

A potential limitation of this study may arise because of the inclusion of wounds with different aetiologies, so any imbalance in the allocation could confound the results. This is important for diabetic foot ulcers and for venous ulcers. This limitation will be managed during the study through balancing the type of wounds included and through subgroup analysis (after data collection).

Thus far, no study has been conducted comparing this new antioxidant dressing with standard dressings to maintain a moist environment. If our results confirm the hypothesis, this randomized clinical trial could help provide new clinical evidence of the efficacy of the antioxidant dressing as an alternative for the treatment of chronic wounds. This study aims to fill some of the gaps in the existing knowledge of advanced therapies for chronic wounds.

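### The primary arm comparisons are valid but unadjusted for baseline, centre or wound type; the promised balancing of wound types has no mechanism; and the Friedman fallback cannot compare arms

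*Protocol article*

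**What the plan says.** All references are to the protocol article.

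- **Outcomes.** There are two primary endpoints, RESVECH 2.0 and wound area. Each is a change between baseline and week 8; for RESVECH it is "score at baseline minus score at 8 weeks".
- **Data analysis plan, primary tests.** Wound area reduction "in the intervention group compared with the standard care group will be tested by a difference of means test". For the scale, "The increase in RESVECH 2.0 [37] score at 8 weeks between both groups will be examined by a difference of means test", by t test or Mann–Whitney depending on normality. No covariate or stratum term is named.
- **Data analysis plan, course over time.** "In addition, a repeated-measures analysis (analysis of variance or Friedman test) and a survival analysis (Kaplan–Meier) will be used" for the evolution over time.
- **Data analysis plan, subgroups.** Subgroup analyses are planned by wound type, to explore whether the effect differs by aetiology, and by centre.
- **Randomization and blinding.** Allocation is made "with a 1:1 allocation ratio", "using stratified block randomization with a fixed block size per centre". Wound type is not a stratification factor.
- **Discussion.** Mixed aetiologies are named as a potential limitation, because an imbalance between arms could confound the results. The stated remedy is: "This limitation will be managed during the study through balancing the type of wounds included and through subgroup analysis (after data collection".

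**The concern.** There are three linked weaknesses.

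1. The primary tests leave out information that the trial already collects. Baseline enters only by subtraction. Centre determines the randomization but is not in the test. Wound type, which the authors themselves see as prognostic, is not in it either. With 54 patients, six named aetiologies and entry areas from 1 to 250 cm², this may cost useful precision. Absolute area reduction is tied closely to baseline size, since a 1 cm² wound cannot shrink by more than 1 cm².
2. The stated remedy for aetiology imbalance does not work as described. Nothing in the allocation scheme balances wound types between arms, and balancing the types that are *included* would not balance them *across arms*. A subgroup analysis asks whether the effect differs by type. It leaves the overall estimate as it was.
3. If the repeated measures are judged non-normal, the named fallback is Friedman. It tests change over visits in one set of patients. A significant result would show that wounds change with time, and a reader could take it for evidence on the dressing.

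**Working it through.** **Step 1. Reproduce the plan's own figures.** Inputs (Sampling section): difference 2 points, SD 2.0, 5% type 1 and 20% type 2 error. A two-sided two-sample t test gives 16.7, so 17 per group. For 49.5 − 30.0 = 19.5 days with SD 20.0 it gives 17.5, so 18. Both stated sizes reproduce, and both rest on an unadjusted comparison. Power at 17 per group is 81%.

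**Step 2. Gain from baseline as a covariate.** Let r be the baseline/week-8 correlation and k the week-8 SD divided by the baseline SD. The document gives neither, so both are assumptions. In large samples

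Var(ANCOVA) / Var(change score) = k²(1 − r²) / (1 + k² − 2rk).

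Denominator minus numerator is (1 − rk)², so the ratio never exceeds 1. With k = 1 it reduces to (1 + r)/2. Taking 2.0 as the SD of the change score (the document does not say whether it is that or the SD of the score):

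| r (assumed), k = 1 | Variance ratio | n per group (unadjusted: 17) | Power at 17 per group (unadjusted: 81%) |
|---|---|---|---|
| 0.3 | 0.65 | 12 | 94% |
| 0.5 | 0.75 | 13 | 90% |
| 0.7 | 0.85 | 15 | 87% |

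With unequal SDs:

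- r = 0.7, k = 1.2: 1.44 × 0.51 / (1 + 1.44 − 1.68) = 0.734/0.76 = 0.97.
- r = 0.5, k = 1.5: 2.25 × 0.75 / (1 + 2.25 − 1.5) = 1.688/1.75 = 0.96.

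The gain therefore ranges from a few percent to about a third.

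**Step 3. Gain from centre and wound type.** If together they explain 10%, 20% or 30% of outcome variance (assumed), power at 17 per group is 85%, 89% or 92%. In a simulation with r = 0.5, equal baseline and residual SDs, 17 per group and a two-level wound type worth 2 points (assumed), power was 72% for the t test on change, 79% for ANCOVA on baseline and 88% for ANCOVA plus wound type. Type I error was 5.1%, 4.8% and 4.4%, so all three are valid.

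**Step 4. Chance imbalance in aetiology.** Table 1 names six types, so 54/6 = 9 patients each if equally common (assumed). With 27 of 54 per arm, and ignoring centre blocks because they do not control wound type, the hypergeometric probability of a 2:1 or worse split is 0.47, 0.29 and 0.33 for a type with 9, 10 and 12 patients. For a type at 30% to 50% prevalence (assumed), a difference of 20 percentage points or more between arms arises in about 14% to 10% of trials.

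The effect on the estimate is modest. A 6 v 3 split is 3/27 = 0.11 of an arm; with a 2-point prognostic difference (assumed) it shifts the estimate by 0.22 points. Splits of 7 v 3 or 8 v 4 shift it by 4/27 × 2 = 0.30. The standard error is 2√(2/27) = 0.54 at 27 per arm and 2√(2/18) = 0.67 at 18. The shift is thus about 0.3 to 0.5 of a standard error.

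**Step 5. Friedman.** Simulation with 27 per arm, five visits and illustrative SDs (1.5 between patients, 1.4 within), 1000 trials per setting:

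| Truth | Friedman rejects | t test between arms rejects |
|---|---|---|
| Arms identical, both improve 4 points | 100% | 4% |
| Arms differ by 2 points, overall mean flat | 4% | 95% |

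Friedman follows the overall time trend and carries no information on the arm contrast.

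**The case against.** The strongest reply is that nothing in the primary analysis is invalid. Randomization justifies an unadjusted t test on change, its ordinary standard error already allows for chance imbalance, and leaving the stratum out tends to make intervals too wide, which is conservative. Covariates are often specified in an analysis plan that is not shown here. The planned sizes already assume the unadjusted test. All of this stands, and it limits the point to efficiency and to what the article itself states: a named test, a remedy without a mechanism, and a fallback with no arm factor.

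Several stronger readings are tempting, and the document does not support them:

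- *Baseline is ignored.* It is not; the endpoint subtracts it. It is only missing as a covariate.
- *Centre and wound type are absent from the plan.* Both have planned subgroup analyses. They are absent from the primary tests.
- *The authors admit an imbalance.* The Discussion speaks of a possible one.
- *The main result rests on Friedman.* It is one option in a supplementary analysis, and the t test or Mann–Whitney does compare arms.
- *Repeated-measures ANOVA must drop every patient with a missed visit.* Where the planned last-observation-carried-forward rule applies, visits are filled. The loss arises only in the branch without imputation.
- *18 patients per arm would act like 21 to 28.* That is 18/0.85 to 18/0.65. It needs equal SDs at both times and largely disappears if the week-8 SD is larger.

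**Conclusion.** The point holds as an improvement that should be made, not as a fatal flaw. The primary comparisons are valid but give up precision: 15% to 35% of variance for correlations of 0.7 down to 0.3 with equal SDs, and possibly only 3% to 4% if the week-8 SD is larger. Correlation, SD ratio and the prognostic strength of wound type are assumptions throughout. In large samples adjustment cannot do worse than the change score.

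Two statements need correcting whatever those values are. The Discussion's remedy for aetiology imbalance is not delivered by the allocation scheme or by subgroup analysis. Friedman cannot serve as a comparison of arms over time.

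**What to change.** 1. **Primary analysis, both endpoints.** Analyse the week-8 RESVECH score and the week-8 wound area by ANCOVA, or by a mixed model with arm, visit and arm-by-visit terms. Adjust for baseline value, centre and wound type. Report the week-8 contrast with its 95% CI. If area is skewed, use a log or other suitable scale fixed in advance; because healed wounds have area zero, the chosen scale must accept zero.
2. **Wound type.** Use a few classes named before unblinding, for example leg or diabetic foot ulcer, pressure ulcer, and dehisced surgical wound.
3. **Course over time.** Remove Friedman and use the arm-by-visit term in its place.
4. **Subgroups.** Test wound class and centre as interactions with arm.
5. **Discussion.** Replace the promise to balance wound types with a statement that the analysis adjusts for wound type.

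The change is to analysis wording only. It needs no added patients, visits or data, since centre and aetiology are already required for the planned subgroups. The price is a few degrees of freedom.

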#### Sampling

Sample size was estimated based on two possible outcomes. First, to detect a difference of 2 points in the RESVECH 2.0 scale mean scores [37] between the intervention and the control group with a standard deviation of 2.0 (5% type 1 error and 20% type 2 error) based on data published by Castro et al. who found a reduction of 8 points in RESVECH 2.0 at 4 weeks of treatment (this is a 23% reduction) [24]. We used a 2-point reduction for sample estimation as the minimum clinically significant difference, and so the study was powered enough to detect just this small difference. The required sample size for this is 17 patients per group. Second, the time to achieve a 50% reduction of the wound area, estimating an average of 49.5 days in the control group and 30.0 days in the intervention group with a standard deviation of 20.0 days (5% type 1 error and 20% type 2 error), as based on the study by Lee [38]. The required sample size for this is 18 patients per group.

An additional 30% is added to compensate possible loss of patients in follow-up, and so the final sample size is 54 patients (27 patients in each group). It is expected that each one of the three health care centres will recruit 18 patients for the study.

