### Data collection and management

Participants eligible for study entry will be given a unique, sequential, centre-specific study identifier. Clinical data will be entered into paper-based case report forms. After each assessment, the data will be handled according to internal procedures and stored in a secure server. These files will be backed-up into a password-protected environment. Hard copies will be stored locally, in compliance with the Spanish Data Protection Law (2018).

Each patient included in the study will be assessed by one clinical nurse at baseline and every 2 weeks (weeks 2, 4, 6 and 8). Figure 1 shows the variables collected at each assessment. The follow-up of patients in both groups will be continued until week 8 or until complete healing of the wound if this occurs earlier. A follow-up of 8 weeks was considered adequate for this study since the main action of the antioxidant dressing being evaluated is to reactivate the healing process by avoiding the excess of ROS; according to a previous study published by Castro et al. [35], a significant number of wounds improved by the fourth week. In order to promote participant retention and complete follow-up, the nurse will monitor patients in the health care centre. Furthermore, the principal investigator will have the primary responsibility for study monitoring; a formal data monitoring committee is not considered necessary because there is no access to protected information and there is no personal information recorded.

To monitor wound healing, several variables will be used: 1) wound area by direct measurement of length and width with a graduated ruler (Kundin method) [39]; 2) wound area estimated using digital photography with Helcos software [40, 41]; this software is an integrated wound management system, which allows for estimation of the wound area and the relative percentage of tissue types in the wound bed (granulation, slough and necrotic tissue); and 3) the RESVECH 2.0 scale score for chronic wound healing [37] (this scale assesses six aspects — wound size, depth/affected tissues, wound edges, type of tissue in the wound bed, exudate and infection/inflammation — with a higher score showing more improvement in the healing process from 0 (the worst possible status of the wound) to 35 points (wound healed)).

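### The primary RESVECH comparison may be a t test or a Mann–Whitney test according to a normality check, yet the trial is sized and its effect reported on means, so the P value may not test the quantity sized

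*Protocol article*

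**What the plan says.** In the protocol article, under Outcomes, the first primary end point is "an increase in the RESVECH 2.0 scale score" from baseline to week 8. Under Data collection and management the scale runs "from 0 (the worst possible status of the wound) to 35 points (wound healed").

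Under Data analysis plan, the "score at 8 weeks between both groups will be examined by a difference of means test". The bracket that follows makes this a two-sample *t* test or a "Mann–Whitney test depending if variables adjust to a normal distribution". The only normality check named in the article is in the same section, in the sentence on descriptive statistics: "normality will be checked with the Shapiro–Wilk test". "The effect size will be estimated by Cohen’s" *d*, whichever test is used. No rank-based effect measure is given for the Mann–Whitney branch.

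Under Sampling, the RESVECH calculation is made "to detect a difference of 2 points in the RESVECH 2.0 scale mean scores", with an SD of 2.0, and the 2 points are called the minimum clinically significant difference.

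**The concern.** The two candidate tests answer different questions. The t test asks whether mean improvement in points differs. The Mann–Whitney test asks whether a patient in one arm tends to rank above a patient in the other. They agree when one arm is a shifted copy of the other. They need not agree when the arms differ in shape or spread, which is possible on a bounded scale where some wounds may heal and others may not respond.

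Sizing, label and effect measure all refer to means, but the P value may not. A reader could be given a significant P value next to a Cohen's d near zero. Equally, a real difference in means could come with a non-significant rank test. Which of the two questions is answered would depend on the trial's own data.

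**Working it through.** **1. The plan's figures.** Inputs from Sampling: difference 2, SD 2.0, 5% type 1 error (taken as two-sided), 80% power. The normal approximation is n = 2(1.960 + 0.842)² × 2²/2² = 15.7, so 16 per group. The exact t-based calculation gives 16.7, so 17, as stated. For time to 50% area reduction (19.5 days, SD 20.0) the exact figure is 17.5, so 18, as stated. Both figures come from a comparison of means. Power for 2 points at SD 2 is 80.7% at 17 per arm and 95.0% at 27.

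**2. The rule as simulated.** Shapiro–Wilk at 0.05 in each arm; if either arm rejects, Mann–Whitney, otherwise the t test. The 0.05 level and testing each arm separately are assumptions, since the article states neither. Sizes are 27 per arm (all randomised) and 19 (27 × 0.7 = 18.9, after the 30% loss). There were 4,000 runs per scenario, so the simulation standard error is about 0.4 points for a rate near 7%.

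**3. Equal means, different shape.** Arm A is normal with mean 8, SD 2. Arm B has 20% non-responders centred at 0 and 80% responders centred at 10, each with within-group SD 2.
- Mean of B: 0.8 × 10 + 0.2 × 0 = 8, the same as A.
- SD of B: √(0.2 × 0.8 × 10² + 2²) = √20 = 4.47, more than twice the planned 2.0.
- Chance that a B patient exceeds an A patient: 0.8 × Φ(2/2.83) + 0.2 × Φ(−8/2.83) = 0.8 × 0.760 + 0.2 × 0.002 = 0.61. The means are equal, but the ranks are not.

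Now shrink B around 8 by 2/4.47 so that its SD is 2. The centres become 4.42 and 8.89, and the within-group SD 0.89. The same chance is 0.8 × Φ(0.89/2.19) + 0.2 × Φ(−3.58/2.19) = 0.8 × 0.658 + 0.2 × 0.051 = 0.54.

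| Arm B | n per arm | Two-step rule | Mann–Whitney alone | t test |
|---|---|---|---|---|
| SD 4.5 | 19 | 20.4% | 20.8% | 5.8% |
| SD 4.5 | 27 | 28.8% | 28.8% | 6.3% |
| SD 2 | 19 | 6.0% | 6.1% | 4.4% |
| SD 2 | 27 | 7.6% | 7.7% | 5.1% |

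Separate runs of these scenarios gave 21% and 28% to 29% at SD 4.5, and between 6.5% and 8% at SD 2. In every row the two-step rule is almost the same as Mann–Whitney alone.

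Other shapes with equal means and SD 2 in both arms, 27 per arm: normal against mildly skewed (gamma, shape 4) 6.2%; normal against exponential 7.8%; opposite mild skews 8.7%; opposite exponential skews 21.3%. The t test gave 5.0% to 6.1%.

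**4. Both arms from one distribution, 27 per arm.** Normal 5.4%; normal rounded to whole points 5.1%; exponential 4.1%; the SD 4.5 mixture in both arms 5.0%.

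**5. A real mean difference.** Non-responders 30% against 10% give means of 7 and 9, with SDs √(0.21 × 100 + 4) = 5.0 and √(0.09 × 100 + 4) = 3.6. At 27 per arm the two-step rule rejects in 24% and the t test in 37%. For a uniform 2-point shift with gamma shape-4 data the order reverses: 71.8% against 67.4% at SD 3, and 96.5% against 94.7% at SD 2.

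**6. Which branch is taken.** At 27 per arm, Mann–Whitney is chosen in 9% of trials with normal data, in 34% with normal data of SD 2 rounded to whole points, and in about 64% when both arms are gamma shape 4.

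**The case against.** Three stronger readings are tempting, and the documents support none of them.

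- **That the test is picked after seeing the results.** The rule is written in advance and the Data analysis plan has a blinded analyst. The choice is data-driven by rule, not discretionary.
- **That the plan carries a false-positive rate of 20% or more.** If the dressing has no effect, both arms share one distribution and the error stays near 5%. In the equal-means scenarios the distributions do differ, so a rejection is a true finding about ranks and a wrong one only if read as a statement about means. The large figures also need strong assumptions: an arm SD of about 4.5 against the planned 2.0, or opposite extreme skews.
- **That the normality pre-test is the cause.** The rule's rates equal those of Mann–Whitney alone, so a fully pre-specified rank test would show the same divergence from means.

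Other points against also stand. The article gives no distribution of RESVECH change and no healing or non-response rate, so unequal shapes are plausible but not established. Shapiro–Wilk appears in the sentence on descriptive summaries; its use to choose the test is the natural reading, not an explicit statement. Its level, and whether arms are pooled, may properly be left to an analysis plan that is not shown. For moderately skewed data with a uniform shift, the two-step rule has slightly more power than the t test.

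What these points leave untouched is that the article itself states the either/or rule, calls both branches a test of means, and pairs either one with mean-based sizing and a mean-based effect size.

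**Conclusion.** The mismatch is real and lies in the article's own text: on one of its two branches, the primary RESVECH P value does not test the quantity that was sized and is reported beside it. Its practical size is uncertain and probably modest. Under the planned SD of 2 with a responder mixture in one arm, the rule rejects equal means in about 6% to 8% of trials. Rates of 20% to 29% need that arm's SD to be about 4.5. The t test rejects in 4% to 6% in these scenarios. The divergence comes from the rank test's different hypothesis, and it is not an inflated type I error under no effect. All of these figures rest on assumed outcome shapes and an assumed 0.05 pre-test level. The point is worth correcting for clarity about what is being estimated; it does not invalidate the design.

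**What to change.** State one primary RESVECH analysis: the difference between arms in mean change from baseline to week 8, by Welch's t test or the equivalent linear model, with a 95% confidence interval in points. Report Mann–Whitney as a labelled sensitivity analysis. Use the normality check only to choose descriptive summaries. The same wording can serve the continuous secondary outcomes, for which the article also leaves the choice between parametric and nonparametric tests open.

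This costs a sentence or two in the analysis plan, to be settled before the data are analysed. The sample size stands, because it was calculated for a comparison of means. The price is a small loss of power if the effect is a uniform shift in skewed data: about 2 to 5 percentage points in the gamma shape-4 example.

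### Two time-to-event secondary outcomes fall under a mean difference test although follow-up stops at day 56; on the plan's own figures 30–37% of controls would have no time to 50% area reduction to average

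*Protocol article*

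**What the plan says.** - **Outcomes.** Two times to an event are listed as secondary: "The secondary outcomes are the time to achieve a 50% reduction in wound area, the time elapsed until removal of nonviable tissue".
- **Data analysis plan, secondary outcomes.** There are two kinds of test. Proportions and categorical variables get a chi-squared test, and "continuous variables will be tested using a mean difference test (parametric or nonparametric". No other method is named for secondary outcomes.
- **Data analysis plan, primary outcome.** After the tests of the two change scores, the plan adds a repeated-measures analysis, and "a survival analysis (Kaplan–Meier) will be used to analyse the evolution over time".
- **Sampling.** One of the two times is used to size the trial: "estimating an average of 49.5 days in the control group and 30.0 days in the intervention group with a standard deviation of 20.0 days", with "5% type 1 error and 20% type 2 error". The result is "The required sample size for this is 18 patients per group". Time to removal of nonviable tissue has no mean, SD or sample size.
- **Data collection and management.** Assessments are at weeks 2, 4, 6 and 8. Follow-up ends at week 8, or at complete healing if that comes first.
- **Missing data.** Analysis is by intention to treat, with last observation carried forward if outcomes are not missing at random. Nothing is said about a wound that has not reached the event when follow-up ends.

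**The concern.** A mean difference test needs a number for every patient. A wound that has not halved in area by day 56 has no event time; all that is known is that the time exceeds 56 days. The same holds for a patient withdrawn earlier. Carrying the last observation forward cannot supply a time for an event that has not happened.

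That leaves the analyst to choose what to enter. Leaving such wounds out removes the slowest healers, who on the plan's assumptions are mostly controls, and departs from intention to treat. Entering day 56 understates the slow times, again mostly in the control arm. Either choice pulls the estimated difference towards zero. Because the plan does not fix the choice, it could be made after the data are seen.

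The sample size for time to 50% area reduction also treats every time as observed, so its stated 80% power refers to an analysis that an 8-week trial cannot carry out.

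**Working it through.** **Inputs.** Means 49.5 and 30.0 days, SD 20.0, 5% type 1 and 20% type 2 error, 18 per group, 27 per group enrolled after a 30% addition (all Sampling). End of follow-up on day 56 and 14-day visits (Data collection and management). The shape of the time distribution is not given. I therefore used four shapes with the stated means and SD.

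**1. Reproduce the stated 18.** Standardised difference d = 19.5/20 = 0.975. A two-sided two-sample t test at 5% with 80% power needs 17.53 per group, so 18. This matches. A one-sided test would need 14. The figure is therefore an uncensored comparison of means.

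**2. Share without the event at day 56, normal model.**
- Control: z = (56 − 49.5)/20 = 0.325, and 1 − Φ(0.325) = 0.373, or 0.373 × 18 = 6.7 of 18 controls.
- Intervention: z = (56 − 30)/20 = 1.30, and 1 − Φ(1.30) = 0.097.

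**3. Effect on the mean difference, normal model.**
- Unreached wounds dropped: E[T | T ≤ 56] = μ − σφ(z)/Φ(z). Control 49.5 − 20 × 0.3784/0.6274 = 37.4. Intervention 30 − 20 × 0.1714/0.9032 = 26.2. Difference 11.2 days.
- Unreached wounds set to 56: E[min(T, 56)] = Φ(z) × E[T | T ≤ 56] + (1 − Φ(z)) × 56. Control 0.627 × 37.44 + 0.373 × 56 = 44.4. Intervention 0.903 × 26.21 + 0.097 × 56 = 29.1. Difference 15.3 days.

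**4. The same under other shapes.**

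| Shape | Event-free at day 56, control | Event-free, intervention | Difference, dropped | Difference, capped |
|---|---|---|---|---|
| Normal | 37.3% | 9.7% | 11.2 d | 15.3 d |
| Weibull | 36.2% | 10.9% | 12.4 d | 15.8 d |
| Gamma | 32.8% | 10.4% | 13.3 d | 15.9 d |
| Lognormal | 30.4% | 9.1% | 13.8 d | 16.1 d |

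The assumed difference is 19.5 days in every row.

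**5. Power by simulation.** 4,000 trials per setting, events dated to the next 14-day visit, two-sided 5%.

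| Shape | t test, unreached dropped, n = 18 | t test, capped at 56, n = 18 | Log-rank, n = 18 | Log-rank, n = 27 |
|---|---|---|---|---|
| Normal | 42% | 73% | 75% | 91% |
| Weibull | 59% | 82% | 75% | 92% |
| Gamma | 75% | 89% | 78% | 92% |
| Lognormal | 83% | 93% | 83% | 94% |

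Allowing for simulation error between runs, log-rank power is about 75–84% at 18 evaluable per group and about 90–95% at 27 per group before losses. The plan's own 30% loss leaves 27 × 0.7 = 18.9 per group, so the first range is the relevant one if losses are as large as allowed for.

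**6. Does the Kaplan–Meier sentence cover it?** It stands among the analyses of the two primary change scores, as an addition, to describe their course over time. It names no event, no censoring rule and no comparison of arms. The next paragraph turns to secondary outcomes and gives them different tests.

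**The case against.** The best defence is that a survival method is planned and merely misplaced. The primary end points are continuous changes with no event time, so the Kaplan–Meier sentence makes most sense for the times to event. A log-rank test and a censoring rule are details that an article may leave to the SAP. This has weight, and it would be wrong to infer that the plan has no survival method. It does not settle the matter, because the article does more than leave a detail open: it assigns continuous secondary outcomes a test that does not suit these two.

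Second, the nonparametric option would allow a rank test with all unreached wounds tied at the worst rank. That needs no event time and performs well: in the same simulation at 18 per group its power is 76% (normal) to 90% (lognormal). This is a defensible analysis, but the plan does not state it. Nor does the plan say that unreached wounds will be dropped or capped, so the bias in the working is what would follow from those choices, not something the plan prescribes.

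Third, a reader might infer that the trial is badly underpowered, or that power for this outcome is about 42%. The documents do not support that. The 42% needs both a normal model, which puts about 7% of intervention times below zero, and the dropping of unreached wounds; the same handling gives 83% with lognormal times. Capping at day 56 biases the difference but costs little power under most shapes, and with a log-rank test the planned numbers are close to adequate.

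Finally, a reader might take both times to be sized as uncensored means. Only the time to 50% area reduction is, so the event-free shares say nothing about removal of nonviable tissue.

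**Conclusion.** The point stands as a should-fix on two secondary outcomes. The test named for continuous secondary outcomes does not fit times that are cut off at day 56 and seen only every 14 days. For time to 50% area reduction, the plan's means and SD imply that about 30–37% of controls and 9–11% of intervention wounds would be without a time. The mean difference would then fall from 19.5 to about 11–14 days if they are dropped, or about 15–16 if capped. A control share above one third holds under normal or Weibull times but not under gamma or lognormal.

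These sizes rest on the stated means and SD being right and on the four shapes tried; losses before day 56 are not modelled. For removal of nonviable tissue the structural problem is the same, but no size can be given. The firm harm is bias and an undefined value for unreached events, rather than a wrong sample size. The primary end points and their tests are not affected.

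**What to change.** **Data analysis plan.** Take both time outcomes out of the mean difference rule. Analyse each with Kaplan–Meier curves by arm and a between-arm log-rank test, censoring wounds without the event at their last assessment, at the latest day 56. Stratifying by centre and adding a hazard ratio suited to 14-day intervals (for example a discrete-time complementary log-log model) are optional. Include in the nonviable-tissue outcome only wounds that have such tissue at baseline.

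**Sampling.** State that the 18 per group assumes uncensored times, and that log-rank power with censoring at 56 days is about 75–84% at 18 evaluable per group and about 90–95% at 27 per group before losses, under the stated means and SD.

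**Cost.** A change of wording in two sections, made before unblinding, and a stated power for this outcome that is a range which may fall slightly below 80%. No new data are needed and the enrolled number stays at 54.
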